### Sample Size

For the calculation of the sample size we make the following assumptions:

• The effect of the standard treatment on the control group will cause an average limb volume reduction of 5%.

• The effect of the treatment on the experimental group will cause an average limb volume reduction of 25%

• We also assume that the standard deviation will be similar in both groups and near to 25%. With this information and with an alpha risk of 0.05 and a power of 0.80, the calculation of the sample size is 20 patients in each group. Considering a 30% dropout rate in each group, the corrected sample size is 58 patients randomized in two groups of 29 patients each.

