#### Efficacy analyses

The analyses of the efficacy will be carried out using common measures such as mean and/or median ratio differences for the quantitative variables and risk ratios (relative risk) and NNT for the quantitative variables.

In all cases, the corresponding confidence intervals will be calculated.

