##### Safety Analyses

Side effects, withdrawal and/or complication rates will be studied in the same way as those described for the quantification of the efficacy in the case of qualitative variables. In all case analyses, the confidence intervals will be also calculated.

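### Risk ratio and NNT with intervals throughout do not suit uncommon side effects, and the NNT often has no single finite interval; a risk difference would serve every binary outcome (minor)

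*Protocol article*

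**What the plan says.** Under Efficacy analyses, the measures named for binary outcomes are "risk ratios (relative risk) and NNT". The text there prints the word for quantitative variables twice. The Safety Analyses section, which refers back to qualitative variables, shows that the second occurrence means qualitative. The same section adds: "In all cases, the corresponding confidence intervals will be calculated".

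Safety Analyses carries these measures over to harms and dropout: "Side effects, withdrawal and/or complication rates will be studied in the same way as those described for the quantification of the efficacy". It repeats the requirement for intervals.

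Statistical methods names risk ratios as the measure for binary effects, with intervals and tests, and allows Fisher's exact test. None of these sections names a risk difference for a binary outcome, and the article gives no expected side-effect rate.

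On size, Sample Size states: "Considering a 30% dropout rate in each group, the corrected sample size is 58 patients randomized in two groups of 29 patients each". The number before inflation is 20 per group. Primary Outcome defines a good response as a reduction of at least 20%.

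**The concern.** Both named measures can break down in small samples.

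- **Risk ratio.** If one arm has no events, the estimate is zero or infinite and the usual log-scale interval cannot be computed. If both arms have none, the ratio is 0/0.
- **NNT.** It is the inverse of the risk difference. When the interval for the difference contains zero, the inverse splits into two ranges joined at infinity, one of benefit and one of harm.

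An interval is promised in every case, and the measures are extended to outcomes where zero counts are likely. At stake is whether the report can say how large a harm the data still allow. With no events in 29 women, the true rate could be as high as 11.9% (exact two-sided 95% limit), and a risk ratio cannot show that.

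**Working it through.** **1. The plan's own sample size.** The inputs from Sample Size are a control mean of 5%, an experimental mean of 25%, an SD near 25%, alpha 0.05, power 0.80 and 30% dropout.

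- n per arm = 2(z_α + z_β)²(SD/difference)² = 2(1.645 + 0.842)²(25/20)² = 19.3, so 20. This reproduces the stated figure with a one-sided 0.05. A two-sided test gives 25. The article does not state sidedness, and the point here does not depend on it.
- 20/(1 − 0.30) = 28.6, so 29 per arm, as stated.

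The checks below therefore use 20 and 29 per arm.

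**2. Side effects: how often an arm is empty.** The article gives no rates, so equal rates p in both arms are assumed.

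P(at least one arm empty) = 1 − [1 − (1 − p)ⁿ]²; P(both empty) = (1 − p)²ⁿ.

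For p = 2% and n = 29: 0.98²⁹ = 0.557, so 1 − 0.443² = 0.80, and 0.557² = 0.31.

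| Assumed rate | n = 29: at least one empty | n = 29: both empty | n = 20: at least one empty | n = 20: both empty |
|---|---|---|---|---|
| 2% | 80% | 31% | 89% | 45% |
| 5% | 40% | 5% | 59% | 13% |
| 10% | 9% | 0.2% | 23% | 1.5% |
| 20% | 0.3% | <0.1% | 2.3% | <0.1% |

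With one empty arm a score interval for the ratio still exists, but it is open or touches zero: 2/29 v 0/29 gives 0.54 to infinity. With both arms empty there is no ratio by any method.

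**3. Good response.** Assume that percentage reduction is normally distributed, and that the limb volume reduction in Sample Size and the lymphoedema reduction in Primary Outcome are on one scale. The response rates at the 20% cut-off are then:

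- experimental: 1 − Φ((20 − 25)/25) = 1 − Φ(−0.2) = 57.9%
- control: 1 − Φ((20 − 5)/25) = 1 − Φ(0.6) = 27.4%

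The risk ratio is 57.9/27.4 = 2.11 and the NNT is 1/0.305 = 3.3.

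An arm without responders occurs in 0.16% of trials at n = 20 (essentially 0.7257²⁰) and 0.01% at n = 29. The risk-ratio interval is therefore almost always available.

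For the NNT, all pairs of binomial counts were enumerated to find how often the 95% interval for the risk difference contains zero:

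| Interval | n = 20 | n = 29 |
|---|---|---|
| Newcombe | 51% | 35% |
| Wald | 41% | 33% |

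For example, 8/20 v 5/20 is a difference of 15 points (NNT 1/0.15 = 6.7), with a Newcombe interval from −13.4 to +40.4 points. Inverted, this runs from 1/0.404 = 2.5 for benefit, through infinity, to 1/0.134 = 7.5 for harm.

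**4. Withdrawal.** At the planned 30% in each arm, an empty arm occurs in 0.2% of trials or fewer, so the risk ratio is usable. The NNT interval is split in 95% of trials with Newcombe intervals at both sizes, and in 93% to 94% with Wald.

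**5. The alternative.** The Newcombe interval for the risk difference was finite in every case tried. For 0/29 v 0/29 the Wilson upper limit in each arm is 3.84/(29 + 3.84) = 0.117, which gives −11.7 to +11.7 points. For 2/29 v 0/29 the interval is −5.8 to +22.0 points.

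The upper limit for 0/29 in one arm is 1 − 0.025^(1/29) = 11.9%.

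**The case against.** The strongest reply is that the list of measures is given as examples. It does not exclude a risk difference, and an NNT with an interval already implies one. The interval method and the handling of zero counts are commonly left to an analysis plan, which is not shown. This stands, and it limits the weight of the point. It does not remove it: no choice of interval method yields a ratio from 0 v 0, or one finite NNT range when the difference spans zero. The difficulty lies in the measures the article does name.

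It is also fair to say that the NNT percentages largely restate limited power. The risk difference carries the same uncertainty; it only displays it as one readable interval. The 51% applies only if outcomes exist for just 20 women per arm. At the 29 randomised it is 35%.

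A reader might go further in three ways that the documents do not support:

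- **That these intervals often do not exist for binary outcomes at large.** For good response, and for withdrawal near 30%, the risk-ratio interval fails in 0.2% of trials or fewer. With one empty arm a score interval is still available, and a split NNT interval can be printed as two ranges.
- **That harms would end up reported by a p-value alone.** Statistical methods calls for effects to be described, with intervals and tests alongside.
- **That an NNT should be quoted only when the interval excludes zero.** That would make reporting depend on significance, which is debatable and not needed here. Nor is the direction of an NNT for harms an error: with the sign reversed, it is a number needed to harm.

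**Conclusion.** The point holds in limited form. The named measures cannot deliver the promised interval for sparse harms. With 29 per arm, at least one arm is empty in 80% of trials at a 2% rate and 40% at 5%, and both are empty in 31% and 5%. These rates are assumed; if side effects run at 20% in both arms, the difficulty nearly vanishes.

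The NNT lacks a single finite interval in 35% to 51% of trials for good response, given normality and a common volume scale, and in about 95% for withdrawal at the plan's own dropout rate. The risk ratio itself is adequate for both of those outcomes.

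Severity is minor. The primary outcome is continuous, and its comparison is untouched.

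**What to change.** In Efficacy analyses and Safety Analyses:

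- Report the risk difference with a 95% score interval (Newcombe or Miettinen-Nurminen) for every binary outcome.
- For side effects and complications, add per-arm counts with exact (Clopper-Pearson) limits.
- Keep the risk ratio for good response.
- Give any NNT as a derived figure beside its risk difference and interval, whether or not that interval contains zero.

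The cost is a few sentences of wording and slightly more analysis work. Design, sample size and data collection do not change.

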##### Quality of Life Analyses

These analyses are carried out using the results of the Spanish validated quality of life questionnaire, EORTC QLQ-C30 version 2.0 for cancer in general, and EORTC QLQ-BR23 breast cancer-specific questionnaire, and they are assessed by the outcomes that the EORTC (European Organization for Research and Treatment of Cancer) allows.

### Subject's Data Protection

The study will strictly comply with the Declaration of Helsinki and the Spanish Data Protection Law (Constitutional law 15/1999 on Protection of Personal Data) and will protect at all times the patients' rights (Law 15/2002). The informed consent from each patient will be obtained and a randomized number will be assigned in order to protect the patient's anonymity.

### Interventions and distribution of tasks

The rehabilitation physician's functions include:

1. Selection call: the physician determines whether the patient meets inclusion criteria and if so, she is randomized into a treatment group. He/she carries out a complete medical history (history and complete physical exam, taking measurements of both upper extremities for the calculation of lymphoedema volume). He/she explains and provides the informed consent and collects the signed copy. He/she gives the quality of life questionnaire to the patient, who will complete it before starting the outpatient treatment.

2. Week 2 of treatment: Examine the patient. Take measurements of the upper extremities. Rule out the existence of treatment-related side effects. Make the request for a lymphoedema garment. Collect the quality of life questionnaires.

3. Week 5 of treatment: Examine the patient. Take measurements of the upper extremities. Rule out the existence of treatment-related side effects. Check the sleeve. Give a compliance diary to the patient.

4. Week 12 of treatment: To examine Explore the patient. Ask about possible complications that may lead to withdrawal from the study. Take measurements of both upper extremities. If the response to the treatment is good, the patient will be encouraged to continue complying with treatment. The patient's diary is reviewed. A second quality of life questionnaire is provided. The treatment is continued at home. If the response to the treatment is poor, the patient is included again in an outpatient treatment for a month so that if the patient has previously received TH now he/she would be treated with TH + DL and if he/she has been previously treated with TH + DL now she would be treated with DL. The patient is examined at week 16. Measurements of the upper extremities are taken. The presence of treatment-related side effects is ruled out.

5. Week 18 of treatment: the patient is examined. Measurements of the upper extremities are taken. The presence of treatment-related side effects is ruled out. The sleeve is reviewed. A second quality of life questionnaire is delivered.

6. Final call: Week 24 of treatment: the patient is examined. The patient is asked about possible complications that may lead to withdrawal from the study. Measures are taken in both upper limbs. The sleeve is reviewed.

At the end of the study, the patient's calendar is collected. The completed Quality of Life questionnaire is collected. Collaboration with the statistics department is carried out for data completion and publication.

The Physiotherapist's tasks include

1. She/he phones the patients of the study and notifies them of the starting of the treatment. She/he randomizes the patients in treatment A or B according to the instructions of the Biomedical Research Foundation.

2. She/he applies the prescribed treatment and instructs patients in the proper execution of exercise and care of the affected limb.

3. She/he makes the appointment with the patients for review in consultation.

4. She/he notifies the physician of any incidents that may occur.

Finally, the BIOMEDICAL RESEARCH FOUNDATION (BRF) randomizes the patients in the two different treatment groups, monitors the study and facilitates statistical analysis of the data and results.

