### Inclusion criteria

• Women older than 18 years treated for unilateral breast cancer with ipsilateral axillary lymphadenectomy.

• Patients with ipsilateral lymphoedema with a limb volume difference of at least 200 ml compared to the lateral member.

• Patients who have finished treatment with radiotherapy and/or chemotherapy at least six months before the study begins.

• Informed consent must be signed

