### Relevance of the project in terms of its bibliometric impact

The systematic review of literature on the management of lymphoedema was limited by the lack of prospective randomized trials evaluating different treatment options. In 2006, a Cochrane systematic review about physical treatments for reducing and controlling lymphoedema of the extremities selects only three of the articles reviewed on the basis that they are randomized controlled trials that had a follow-up period of at least six months. However, because they did not study the same treatment intervention, the data could not be subsequently pooled. Some evidence suggests that treatment involving a combination of MLD and compression therapy yields reduced oedema volume compared to compression therapy alone if volume is measured directly after the conclusion of MLD (Evidence grade 3 = limited scientific evidence). The existing randomized clinical trials are conducted with small samples and only a few studies include long term monitorization. None of the studies performed are blind and only rarely is an analysis of the rate of "lost to follow-up" patients performed. Before this therapy can be recommended, more randomized controlled trials with an adequate sample size, where MLD short-term and long-term treatment effects could be more closely studied, are needed (SBU Alert Report 2005-04. http://www.SBU.SE/ALERT).

Moreover, groups of experts have highlighted the lack of interest in researching the impact of the physical and psychosocial difficulties of these patients and their quality of life. In conclusion, the need for performing well-designed, randomized trials of the physical treatments and their health impact is a priority.

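### The task list writes randomisation ahead of consent and baseline arm measurement, against the inclusion criteria, and leaves unsettled who allocates, when, and whether the measuring physician knows the arm

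*Protocol article*

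**What the plan says.** All places are in the protocol article.

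- **Order.** Interventions and distribution of tasks lists the rehabilitation physician's functions by visit: selection, then weeks 2, 5, 12, 18 and 24. At selection, "the physician determines whether the patient meets inclusion criteria and if so, she is randomized into a treatment group". The next sentence covers the history and examination, including "taking measurements of both upper extremities for the calculation of lymphoedema volume". Then comes consent: "He/she explains and provides the informed consent and collects the signed copy". The baseline questionnaire comes last.
- **Eligibility.** Inclusion criteria contains "Informed consent must be signed" and "Patients with ipsilateral lymphoedema with a limb volume difference of at least 200 ml compared to the lateral member".
- **Who randomises.** The physiotherapist's first task is to phone patients about the start of treatment, and then: "She/he randomizes the patients in treatment A or B according to the instructions of the Biomedical Research Foundation". The second task is to apply the treatment. The section ends by saying that the Foundation "randomizes the patients in the two different treatment groups, monitors the study".
- **Who measures.** Arm measurements at weeks 2, 5, 12, 16, 18 and 24 are listed among the physician's functions. The week-12 function also covers judging response and, after a poor response, a further treatment month whose content depends on what the patient received before.
- **Masking.** The article does not say whether the physician is masked. On earlier trials, the Discussion remarks: "None of the studies performed are blind".

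**The concern.** Consent and the 200 ml difference decide whether a patient is eligible, so neither can follow a step that depends on eligibility. If site staff follow the written order, two things become possible. Patients could be enrolled selectively or refuse after allocation, and with 29 per group few such losses can be absorbed. The baseline tape measurement could also be taken by someone who knows the arm, and that measurement both admits the patient and serves as the baseline for percentage reduction.

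The second issue is control of the allocation. It is attributed to the person who delivers the treatment as well as to the Foundation, and placed at what look like two different times. If it happens at the selection visit, the recruiting and measuring physician may learn it there.

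The third issue is outcome assessment. Circumference measurement depends on the measurer, and the same physician has an arm-dependent step at week 12. Knowledge of the arm could then influence both the later volumes and the judgement of response.

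**Working it through.** The plan gives no figure for this point, so the check is mainly a comparison of sections.

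**1. Order.** Inclusion criteria requires signed consent and a difference of at least 200 ml. The physician's first task makes randomisation conditional on meeting the criteria, then lists arm measurement and consent. Two readings are possible:
- Sentence order is time order. Randomisation then precedes two of its own conditions, and the sections contradict each other.
- Sentence order carries no meaning. Consent and measurement then come first, but the text does not say so. The list around it runs by visit, and the sentence itself is sequential: criteria met, then randomised.

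Under either reading the text needs to be reconciled.

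**2. Who and when.** There are three mentions and two named parties:

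| Place | Party named | Apparent timing |
|---|---|---|
| Physician's task 1 | none (passive) | selection visit |
| Physiotherapist's task 1 | physiotherapist, on the Foundation's instructions | listed with the call about starting treatment |
| Closing sentence of the section | Foundation | not given |

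**3. Knowledge of the arm.** The week-12 step cannot be carried out without knowing the earlier treatment. If the physician carries it out, the arm is known by then at the latest, and so for the measurements at weeks 16, 18 and 24. At weeks 2 and 5 the inference is weaker. Under Treatment groups both arms have the same bandage, sleeve and exercises, so the garment request and sleeve check do not reveal the arm. It becomes strong at those visits only if allocation takes place at the selection visit.

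**4. Illustrative size.** From Sample Size, the planned difference is 25% − 5% = 20 points. Let B be the baseline volume and e an error in the follow-up volume. The shift in one patient's percentage reduction is 100 × e / B. The value e = 20 ml is assumed; the shift is proportional to e.

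| Denominator B | Shift for e = 20 ml |
|---|---|
| 200 ml excess (entry minimum) | 100 × 20/200 = 10 points |
| 400 ml excess | 100 × 20/400 = 5 points |
| 2000 ml whole limb (assumed) | 100 × 20/2000 = 1 point |
| 3000 ml whole limb (assumed) | 100 × 20/3000 = 0.7 points |

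An error in the baseline acts differently. With a follow-up excess of 150 ml (assumed), a true baseline of 200 ml gives (200 − 150)/200 = 25.0%. A recorded baseline of 220 ml gives (220 − 150)/220 = 31.8%, a shift of 6.8 points.

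For the response rule in Primary Outcome, 20% of a 200 ml excess is 0.20 × 200 = 40 ml. A 20 ml error is half of that margin.

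**The case against.** The strongest defence is that the article never plans to randomise before consent. Randomisation is conditional on the inclusion criteria, and those contain consent and the volume difference. The sentences that follow list functions without any word such as then or after. The physiotherapist's call also fits allocation after the selection visit. This stands to the extent that a reader might infer a settled plan to randomise first and obtain consent later, and the document does not support that. It does not remove the conflict between the written order and the criteria.

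A reader might also infer that three parties randomise independently. The physician sentence is passive, and the physiotherapist acts on the Foundation's instructions, so the mentions may describe one chain: the physician declares eligibility, the Foundation allocates and the physiotherapist implements. That stands. The timing and the wording remain unsettled.

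A reader might further infer that the outcome assessor is unblinded throughout, or that the trial breaks a promise of blinding. Neither is stated. Knowledge of the arm is an inference from the week-12 step, and week 5, the first measurement after the four-week treatment, comes before it. An article's silence on masking is not an error. The Discussion remark describes earlier trials, and this trial does not claim to be blind.

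Finally, the 10-point figure must not be read as half of the planned effect lost. It concerns one patient at the entry minimum, with an assumed error and excess volume as denominator. A bias of that size in the group mean would need errors of that size, in the same direction, in patients near 200 ml. The abstract and Sample Size speak of arm or limb volume, and on a whole-limb denominator the shift is 1 point or less.

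**Conclusion.** The point holds as a contradiction to be reconciled, with a risk of bias if the text is followed literally. The task list puts randomisation ahead of consent and baseline measurement, against the inclusion criteria. Randomisation is attributed to both the treating physiotherapist and the Foundation, at apparently different times. The physician listed for all follow-up volumes also has an arm-dependent step at week 12. This implies, but does not establish, knowledge of the arm from week 12 at the latest, and earlier if allocation occurs at the selection visit.

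The document supports no estimate of mean bias. The single-patient range runs from under 1 point to 10 points, depending on the denominator and on the assumed 20 ml error. The change is worth making because it is specific and cheap and removes an avoidable route to bias in a trial of 58 patients.

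**What to change.** Reconcile Inclusion criteria with Interventions and distribution of tasks so that both give one order:

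1. Signed consent.
2. Measurement of both arms and confirmation of eligibility.
3. Baseline questionnaire completed.
4. Randomisation.

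State that the Foundation generates the allocation and releases it only once the baseline data are recorded. Reword the physiotherapist's task so that this person receives the allocation rather than randomises, and move the passive randomisation clause in the physician's first task to step 4.

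State that at each visit the physician measures and records the volume and the response (reduction of 20% or more, or not) before the arm is disclosed. The week-12 clinical rule stays as it is; only the recording comes before disclosure.

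The cost is a re-ordering of tasks among existing staff and some effort to keep the measuring physician unaware of the arm. Occasional unblinding by patients, or after the week-12 step, has to be accepted.

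### The scheduled side-effect checks seek only treatment-related events, with no stated blinding of the physician who judges, so the side-effect part of the between-arm safety comparison is open to bias

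*Protocol article*

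**What the plan says.** All references are to the protocol article.

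- **Scheduled side-effect checks** (*Interventions and distribution of tasks*). At weeks 2 and 5 the rehabilitation physician's instruction is "Rule out the existence of treatment-related side effects". At week 16 (re-treated patients only) and week 18 it is "The presence of treatment-related side effects is ruled out".
- **Other routes to harm data** (same section). The week 12 instruction is "Ask about possible complications that may lead to withdrawal from the study", and week 24 is similar. For the physiotherapist, the text says "She/he notifies the physician of any incidents that may occur".
- **Who judges** (same section). No blinding of the physician is stated. At week 12 the physician's tasks include re-treating poor responders according to what they had before: "if the patient has previously received TH now he/she would be treated with TH + DL".
- **What treatment means** (*Treatment groups*). Both groups receive exercises, preventive measures, daily multilayer bandage and sleeve. Group B receives MLD in addition.
- **Analysis** (*Safety Analyses*). "Side effects, withdrawal and/or complication rates will be studied in the same way as those described for the quantification of the efficacy", with confidence intervals. The efficacy measures for proportions are "risk ratios (relative risk) and NNT" (*Efficacy analyses*).

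**The concern.** Randomisation makes the arms comparable for all events that occur. It gives no such assurance for events that first pass a causal judgement, if that judgement is made against each arm's own treatment by someone who may know the arm. In group B the physician has one more candidate cause than in group A. Pain or a skin infection could be put down to MLD in group B and to the underlying lymphoedema in group A. A physician who regards MLD as harmless could lean the other way.

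The side-effect risk ratio could then move away from 1 when true rates are equal, or sit near 1 when they differ. The confidence interval would show neither, because it reflects sampling error only. Events passed over at a visit cannot reliably be recovered at analysis, so a later analysis plan could not repair this. The article's Discussion links provision of MLD in health centres to the trial's result, so the harm side of that result matters even though it is not the primary outcome.

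**Working it through.** **1. Is there a stated filter?** Yes. All four visits at which side effects as such are sought (weeks 2, 5, 16 and 18) are worded to look for treatment-related ones. The point rests on these words, not on a missing definition.

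**2. Can the filter differ between arms?** Yes. The arms differ by MLD, and the article itself offers competing explanations for similar events. *Background* lists pain and recurrent infection among the problems of lymphoedema. *Exclusion criteria* lists skin and venous conditions among the contraindications to MLD. The shared bandage, sleeve and exercise narrow the difference, since they are candidate causes in both arms.

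**3. Does the physician know the arm?** By week 12 this is a firm inference, because the switching task needs the previous treatment. Weeks 16 and 18 follow from that. For weeks 2 and 5 it is not established; the article is silent on blinding.

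**4. Do the other routes fill the gap?** Only in part. The question at weeks 12 and 24 is limited to complications that might end participation. The physiotherapist's route is unfiltered but depends on incidents as they arise, and it leads to the same physician.

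**5. Effect on the risk ratio.** The plan states no side-effect rate, so there is no figure to reproduce. The only document input is 29 patients per arm. Let *p* be the true event rate, equal in both arms, and *a*_A and *a*_B the fractions of events attributed to treatment in groups A and B, with each patient counted at most once.

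- Expected recorded rates: *p* × *a*_A and *p* × *a*_B.
- Expected risk ratio (B to A): (*p* × *a*_B) / (*p* × *a*_A) = *a*_B / *a*_A. The true rate cancels.

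With *p* = 0.20 (all rates and fractions are assumptions):

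| *a*_A | *a*_B | Recorded, A | Recorded, B | Risk ratio |
|---|---|---|---|---|
| 1.00 | 1.00 | 0.20 | 0.20 | 1.0 |
| 0.50 | 0.60 | 0.10 | 0.12 | 1.2 |
| 0.70 | 0.90 | 0.14 | 0.18 | 1.29 |
| 0.50 | 0.70 | 0.10 | 0.14 | 1.4 |
| 0.50 | 0.80 | 0.10 | 0.16 | 1.6 |
| 0.50 | 1.00 | 0.10 | 0.20 | 2.0 |

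Swapping the fractions between arms inverts the ratio: 1/1.2 = 0.83, 1/1.4 = 0.71, 1/1.6 = 0.63. If the true rates differ, the recorded ratio is the true ratio times *a*_B / *a*_A. A true ratio of 1.6 with *a*_B / *a*_A = 0.50/0.80 = 0.625 would be recorded as 1.6 × 0.625 = 1.0.

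**6. Effect on a test.** Probability that a two-sided Fisher test at 0.05 rejects, with 29 per arm and equal true rates:

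| Attribution, B against A | *p* = 10% | 20% | 30% | 50% |
|---|---|---|---|---|
| 100% against 100% | 0.009 | 0.021 | 0.025 | 0.025 |
| 90% against 70% | 0.007 | 0.027 | 0.044 | 0.070 |
| 100% against 50% | 0.017 | 0.089 | 0.180 | 0.390 |

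False rejection becomes substantial only with very unequal attribution and common events. The point estimate is shifted in every row with unequal attribution.

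**The case against.** A reader might infer that the trial looks for harm only where it is treatment-related, that a physician who knows the arm decides this throughout, and that the harm comparison is therefore biased. The article does not support that reading:

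- **Harm capture is wider than the four checks.** Withdrawals, the complications asked about at weeks 12 and 24, and the physiotherapist's incident reports carry no relatedness test. The *Safety Analyses* section is not limited to related events. Only the side-effect component is exposed. Arm pain is also covered without any causal judgement, as a patient-reported secondary outcome in both arms.
- **Knowledge of the arm is inferred.** It is not shown for weeks 2 and 5.
- **Unequal attribution is possible, not demonstrated.** Both arms receive the same instruction and share most of the treatment. The term side effect already implies a link to treatment, so the qualifier may be loose wording and not a formal causality rule.
- **Sampling error is larger than the moderate cases.** At recorded rates of 10% and 16%, 29 per arm gives 29 × 0.10 = 2.9 and 29 × 0.16 = 4.6 expected events. The approximate 95% interval around a ratio of 1.6 is 0.4 to 6.3.
- **This is a condensed article.** Event definitions and causality rules may be in the full protocol, and their absence here is no fault.

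All of this limits the claim: open to bias is supportable, biased is not. The core remains. The only scheduled enquiries about side effects as such are worded with a causal restriction, and a between-arm risk ratio is planned on the result. A fuller definition of relatedness would not remove a restriction that is applied against a different treatment in each arm. Low precision does not excuse a shift that the interval cannot show.

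**Conclusion.** The point holds in a limited form. The wording at weeks 2, 5, 16 and 18 puts a causal judgement ahead of a randomised comparison of side effects, and the arms differ in what can be blamed. Direction and size are unknown. The expected distortion is a factor equal to the ratio of attribution fractions, and there is none if attribution is equal in the two arms. The illustrative range of 0.63 to 2.0 rests wholly on assumed fractions; nothing in the documents fixes it.

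Withdrawals, complications and physiotherapist-reported incidents are not affected in this way, and neither is the primary outcome or the sample size. This is a minor, inexpensive improvement to a secondary safety analysis.

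**What to change.** 1. In *Interventions and distribution of tasks*, replace the search for treatment-related side effects with the recording of all adverse events whatever the presumed cause. Ask in the same way in both arms, at each visit that already takes place, and enter relatedness in a separate field.
2. In *Safety Analyses*, make the between-arm comparison on all events. Show events before the week 12 switch separately from those after it, since a re-treated patient has by then had a further course according to her previous treatment. Report treatment-related events as a secondary description only.

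With all events recorded equally in both arms and equal true rates, the expected risk ratio returns to 1.0. The change does not by itself give a clean comparison of the regimens after the switch, which is why the two periods should be shown apart.

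Cost: a wording change in two sections and a short common checklist. The downside is a few more events to record and a higher event count in both arms. The change has to be made in the visit instructions; the analysis plan alone comes too late.
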